#### Muscle strength

*Quadriceps:* Maximum voluntary isometric strength of the knee extensors will be assessed on an isokinetic dynamometer (HUMAC, CSMI, Boston) with the knee at 90 degrees of knee flexion [40]. Maximum torque reached over 3 repetitions of 3 s each will be recorded and normalised to body mass (Nm/kg).*Hip abductors:* Maximum voluntary isometric strength of the hip abductors recorded using a handheld dynamometer (Lafayette Manual Muscle Test System, Lafayette, Indiana) with the hip in neutral abduction will be assessed. Average force from 2 repetitions of 3 s each will be recorded, converted to torque and normalised to body mass (Nm/kg) [25, 41].

#### Additional measures

##### Co-intervention use

Medications for knee pain and other treatments for knee OA will be recorded at baseline and 12 weeks. Participants will complete a custom-developed table about the frequency of use (over the past 6 months at baseline and the past 12 weeks at follow up) of a number of pain and arthritis medications and co-interventions.

##### Adverse events

These will be ascertained by questionnaire at 12 weeks and defined as any problem that participants believe was caused by the exercise program that required them to seek treatment and/or lasted for two or more days.

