### Data collection and management

Data will be obtained via online questionnaires (or paper-based if requested). Data will be stored in secure electronic databases and de-identified. Some data (i.e. Physiotherapists’ treatment notes) will be stored either in hard copy or electronically on the premises of the treating physiotherapist. Offsite storage will be in accordance with the protocols for maintaining security and privacy of data and will be password protected. Once completed, the notes will be mailed/emailed to researchers to be stored securely. All authors will have access to the final trial dataset.

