### Interventions

Seven physiotherapists in seven private practices at various locations throughout Melbourne, Australia will deliver both interventions. The physiotherapists have an average of 15.1 (range 6–28) years of clinical experience since qualification and 10.6 (range 3–23) years of post-graduate clinical musculoskeletal experience. Six (85%) have formal postgraduate Masters qualifications in sports or manipulative/musculoskeletal therapy. All physiotherapists will attend a 4-h training session and be provided with a treatment manual describing the interventions. Regular telephone meetings will be conducted with the physiotherapists to reinforce the protocol and discuss any study issues. This will help to ensure similar treatment administration among the therapists. Weights and elastic bands will be provided to the physiotherapist to give to the study participants.

Participants in both groups will visit a physiotherapist for an individual session five times over 12 weeks (approximately study weeks 1, 2, 4, 7 and 10). Each session will last 30–40 min. In our previous study, participants visited the physiotherapist on 14 occasions over 12 weeks [11]. However we reduced this to five sessions in the current study for several reasons. First, informal feedback from participants was that the number of sessions was excessive. Second, our other exercise studies in patients with knee OA have shown comparable adherence with fewer sessions [22, 23]. Third, five sessions is a more realistic number to generalise to real life clinical practice. The physiotherapist will teach the participant an exercise program which they will be asked to perform at home four times per week. At the scheduled sessions, the physiotherapist will conduct a brief reassessment to determine progress and any adverse effects and will watch the participant complete the program in order to review and correct quality and form of exercise performance. Findings will help determine physiotherapists’ decision-making regarding progression or modification of the exercises. Participants will be asked to record their exercise completions in a log book. The physiotherapists will check the participants’ log book and set goals/targets to help maintain adherence and motivation. Both groups will also receive a one-page sheet providing information about OA.

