### Trial sample size

The sample size was calculated based on both primary outcomes of pain and function. For an effect size of 0.5, power 80% and two-sided significance level 0.05, with a correlation between pre- and post-measurements of 0.45 for pain [11], 51 participants per arm will be required (using analysis of covariance including baseline pain measurement as a covariate). To account for 20% loss to follow up, sample size will be increased to 64 per arm, for a total of 128. This gives power of 83% to detect an effect size of 0.5 for function with a correlation between pre- and post-measurements of 0.49 [11] and a two-sided significance level of 0.05.

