### Monitoring

Fortnightly meetings will be held between the trial coordinator and the lead investigators to monitor adverse events, and/or any problems that may arise during the course of the trial and to review recruitment targets and timelines. Regular contact between the investigators and the physiotherapists will monitor any problems arising with implementation of the interventions.

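### The reported adverse-event outcome rests solely on a 12-week self-attribution questionnaire, and nothing routes the harms physiotherapists look for at each session into the arm comparison

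*Protocol article*

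**What the plan says.** The protocol article sets source, timing and definition together under Adverse events: "These will be ascertained by questionnaire at 12 weeks and defined as any problem that participants believe was caused by the exercise program". A severity threshold follows: "that required them to seek treatment and/or lasted for two or more days". No other source is named there.

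Three other sections describe information on harms that arises during the trial:

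- **Interventions:** at the five scheduled visits (about weeks 1, 2, 4, 7 and 10), "the physiotherapist will conduct a brief reassessment to determine progress and any adverse effects".
- **Data collection and management**, on the physiotherapists' treatment notes: "Once completed, the notes will be mailed/emailed to researchers to be stored securely".
- **Monitoring:** "Fortnightly meetings will be held between the trial coordinator and the lead investigators to monitor adverse events".

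The section on the number of physiotherapy sessions attended names the treatment notes as its data source. That is the only research use of the notes that the article states. Trial sample size gives the allowance for attrition: "To account for 20% loss to follow up, sample size will be increased to 64 per arm, for a total of 128".

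**The concern.** A harms outcome collected once, at the end, depends on the participant still being reachable and willing to answer. People who stop because the exercise aggravated their knee may be over-represented among those who do not answer. The outcome would then be most incomplete where it is most informative.

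This matters in TARGET because the Background rests partly on tolerability. It speculates that the weight bearing program is more demanding and loads the knee more in people with obesity. If one program is less well tolerated and this leads to drop-out, the questionnaire counts could understate harms more in that arm. The trial already gathers information that could show this, but the article does not say that it will be used.

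**Working it through.** **1. The plan's own figures.** Inputs from Trial sample size: effect size 0.5, power 80%, two-sided 0.05, pre-post correlation 0.45 for pain.

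- n per arm = 2(1 − r²)(z₀.₉₇₅ + z₀.₈₀)² / d² = 2 × 0.7975 × 7.849 / 0.25 = 50.1, rounded up to 51. This matches.
- Allowance for loss: 51 / (1 − 0.20) = 63.75, rounded up to 64 per arm and 128 in total. This matches.
- Function, r = 0.49, 51 per arm: power 82.6% by the normal approximation, against 83% stated. This agrees.

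The sample size is not in dispute. It is used only for the attrition figure.

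**2. Participants outside the harms outcome.** 0.20 × 128 = 25.6, or equivalently 128 − 2 × 51 = 26. That is about 13 per arm if loss is equal.

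**3. Does any section bring these people back in?**

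| Section | Information on harms | Said to enter the reported outcome? |
|---|---|---|
| Adverse events | 12-week questionnaire, self-attributed, with threshold | Yes, and it is the only source named |
| Interventions | Check at each of five sessions | Not stated |
| Data collection and management | Treatment notes sent to researchers | Not stated |
| Number of physiotherapy sessions attended | Treatment notes | Used for attendance |
| Monitoring | Fortnightly review of adverse events | Not stated |

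The Statistical analysis section works from all available data from randomised participants. For an outcome defined by one questionnaire, that means the responders.

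**4. How much could be uncounted?** The article gives no event rates, so this part is assumption. Let p be the event rate in responders and kp the rate in the 20% who do not respond. The share of affected participants left uncounted is 0.2k / (0.8 + 0.2k), whatever p is:

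- k = 1: 0.2 / 1.0 = 20%
- k = 2: 0.4 / 1.2 = 33%
- k = 3: 0.6 / 1.4 = 43%

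Uncounted people number 25.6 × kp. For p from 10% to 30%, that is about 3 to 8 at k = 1 and about 8 to 23 at k = 3.

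**5. Effect on the arm comparison.** Suppose responders in both arms report 15%, non-responders in one arm also have 15%, and non-responders in the other have 40% or 60% (all assumed). The true difference is 0.2 × (40% − 15%) = 5 points or 0.2 × (60% − 15%) = 9 points, while the reported difference is zero. With k equal in both arms and equal loss, the reported rates still differ in the right direction. Bias in the comparison therefore needs loss or excess risk to differ by arm.

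**The case against.** The strongest reply is that the trial is not blind to harms before week 12. Physiotherapists look for them, investigators stay in regular contact with the physiotherapists, fortnightly meetings review them, and allocation can be unblinded for unexpected events. A reader might infer that harms in people who drop out go wholly unnoticed, or that the fortnightly meetings cannot function because the questionnaire comes only at the end. The article supports neither reading. It does not say that the meetings rely on the questionnaire, and safety monitoring and a standardised end-of-trial outcome can coexist.

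Other parts of the reply also stand:

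- The 20% is a planning allowance, not a forecast of questionnaire non-response. Questionnaires are online or on paper, so someone who stops exercising or does not return to the laboratory can still answer.
- Both programs may be modified or paused for pain, so a flare does not imply withdrawal.
- Adverse events are an additional measure with no hypothesis attached. Even with full capture, 64 per arm gives low power for differences of the size illustrated: about 11% for 15% against 20%, and 25% for 15% against 24% (normal approximation, two-sided 0.05).
- Self-attribution with a threshold is a workable definition, the same in both arms, and is applied to participants blinded to the hypotheses. Replacing it with all-cause capture would be a preference rather than a correction.

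It could also be said that a condensed article leaves such routing to the full protocol. That carries less weight here. The article states the collection rule outright, and it names the treatment notes as a source where it intends to use them, for attendance. None of the reply supplies a route from visit findings to the harms reported by arm.

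**Conclusion.** The point holds for the reported adverse-event outcome, not for the trial's awareness of harms. As written, anyone who does not complete the 12-week questionnaire is outside the harms comparison: about 26 of 128 if non-response equals the 20% allowance, and fewer if people who stop still answer. Information gathered at the five sessions and at the fortnightly meetings has no stated place in that comparison.

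Whether this biases the comparison depends on drop-out related to harm differing by arm, which the article can neither show nor exclude. A reader might infer a definite bias towards no difference, or take the 5 to 9 point illustration as an estimate. Both go beyond the documents, because every event rate used is assumed and the true size is unknown. The primary outcomes and the sample size are unaffected.

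**What to change.** Keep the 12-week questionnaire and its definition. Add a second source and state how it is reported, for example:

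*Events recorded in the physiotherapist treatment notes, and at withdrawal where a participant gives a reason, that meet the same treatment or two-day threshold will be abstracted for all randomised participants. They will be reported by arm, separately from the questionnaire counts, together with the number of questionnaire non-responders in each arm.*

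Reconcile the Adverse events, Interventions, Data collection and management, and Monitoring sections so that each says whether its information feeds the reported outcome or serves oversight only.

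The cost is abstraction of notes the researchers already receive and a field to record any reason given at withdrawal. There are two limits. The notes are written by physiotherapists who know the allocation and deliver both programs, so the two sources should be shown side by side and not merged. The notes also stop at the last session attended, so they narrow the gap for people who leave early without closing it.

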##### Adherence

Adherence to the prescribed home exercise program will be self-reported and measured in three ways: i) using an 11-point NRS scale from “strongly disagree” to “strongly agree”, participants will rate to what extent they agree with three statements (“I have been doing my exercise sessions 4 times each week as recommended”; “Within each exercise session, I have been doing all of the exercises recommended (e.g. 5 different exercises)”; “For each exercise, I have been doing the number of repetitions recommended (e.g. ten times each)”); ii) Number of prescribed exercise sessions completed in the last week measured at 12 weeks with scores ranging from zero to four; iii) Exercise Adherence Rating Scale (EARS) Section B [42]. Scores range from 0 to 42, with higher scores indicating better adherence.

##### Number of physiotherapy sessions attended

This will be collected from the physiotherapist treatment notes.

#### Other measures

A range of other measures will be collected for subsequent analyses of potential moderators and mediators of clinical effects. These measures will not be used to determine treatment efficacy. The measures include: physical activity levels using the Physical Activity Scale for the Elderly [43]; self-efficacy using the Arthritis Self Efficacy Scale [44]; kinesiophobia measured with the Brief Fear of Movement Scale for OA [45]; pain catastrophising using the Pain Catastrophising Scale [46]; emotional state using the Depression, Anxiety, and Stress Scale (DASS-21, [47]); number of knee pain zones assessed using the Photographic Knee Pain Map [48]; pain while performing exercises assessed using an 11-point NRS; knee confidence and knee stability each scored on a 5-point Likert scale.

### Trial sample size

The sample size was calculated based on both primary outcomes of pain and function. For an effect size of 0.5, power 80% and two-sided significance level 0.05, with a correlation between pre- and post-measurements of 0.45 for pain [11], 51 participants per arm will be required (using analysis of covariance including baseline pain measurement as a covariate). To account for 20% loss to follow up, sample size will be increased to 64 per arm, for a total of 128. This gives power of 83% to detect an effect size of 0.5 for function with a correlation between pre- and post-measurements of 0.49 [11] and a two-sided significance level of 0.05.

### Monitoring

Fortnightly meetings will be held between the trial coordinator and the lead investigators to monitor adverse events, and/or any problems that may arise during the course of the trial and to review recruitment targets and timelines. Regular contact between the investigators and the physiotherapists will monitor any problems arising with implementation of the interventions.

### Dissemination plans

Findings of the RCT will be presented at relevant conferences and published in a relevant peer-reviewed journal. Participants with knee OA will be provided with a lay summary of findings. Findings will also be disseminated through the networks of the Centre for Health, Exercise and Sports Medicine, and the National Health and Medical Research Council Centre for Research Excellence in Translational Research in Musculoskeletal Pain.

## Discussion

This trial will provide evidence to show whether there is a difference in clinical outcomes following two different types of exercise programs in people with medial knee OA and concomitant obesity, a common knee OA subgroup. Specifically, it will either prove or disprove the hypothesis that greater benefits will be found with non-weight bearing quadriceps strengthening exercise than with weight bearing functional exercise when applied to this group. The study will help inform exercise prescription recommendations for people with medial knee OA and obesity.

## Data Availability

Not applicable.

## Abbreviations

AQoL 6D: Assessment of Quality of Life Instrument
BMI: Body mass index
CONSORT: Consolidated Standards of Reporting Trials
DASS-21: Depression, Anxiety, and Stress Scale
EARS: Exercise Adherence Rating Scale
HREC: Human Research Ethics Committee
KOOS: Knee Injury and Osteoarthritis Outcome Score
NRS: Numeric rating scale
NWBE: Non-weight bearing quadriceps strengthening exercise program
OA: Osteoarthritis
RCT: Randomised controlled trial
TIDieR: Template for Intervention Description and Replication
WBE: Weight bearing functional exercise program
WOMAC: Western Ontario and McMaster Universities Osteoarthritis Index
